## **8. Data analysis**

### **8.1 Calculation of study numbers**

The objective of this study is to assess the efficacy of two different treatment regimens as compared to current general practice. The primary analysis will be the comparison of the duration of antibiotic

treatment of the CRP-guided treatment group compared to common practice and of the PCT-guided treatment group compared to common practice in the intent-to-treat (ITT) population. A per-protocol analysis will be performed as well.

We used the criteria mentioned above for CRP and PCT (procalcitonin level below 0.25 mcg/L **or** a reduction to 10% of the initial value; CRP below 100 mg/L **and** a reduction to 50% of the initial value) to retrospectively perform an analysis on the database from the CAPISCE trial to predict a mean and a standard deviation of antibiotic treatment for both groups in order to perform the power analysis. We then retrospectively selected 170 cases from the CAP-START trial to derive a mean and standard deviation for the common clinical practice group. The results of all groups are listed below:

| Duration of theoretical antibiotic treatment in the CRP guided group |     |         |         |        |                |
|-----------------------------------------------------------------------------|-----|---------|---------|--------|----------------|
|                                                                             | N   | Minimum | Maximum | Mean   | Std. Deviation |
| crpdag                                                                      | 196 | 1,00    | 14,00   | 5,1327 | 3,61518        |

| Duration of theoretical antibiotic treatment in the PCT guided group |     |         |         |        |                |
|-----------------------------------------------------------------------------|-----|---------|---------|--------|----------------|
|                                                                             | N   | Minimum | Maximum | Mean   | Std. Deviation |
| pctdag                                                                      | 173 | 1,00    | 14,00   | 6,2832 | 4,80257        |

| Duration of antibiotic treatment in the Common Clinical Practice group |     |         |         |        |                |
|-------------------------------------------------------------------------------|-----|---------|---------|--------|----------------|
|                                                                               | N   | Minimum | Maximum | Mean   | Std. Deviation |
| dag                                                                           | 170 | 0,00    | 42,00   | 8,7588 | 5,87499        |

We assume a mean difference of 2 days of antibiotic treatment to be clinically relevant. The results will be evaluated for a normal distribution using the kolmogorov-smirnov test. If they are normally distributed an ANOVA will be performed, with the addition of a Tukey-HSD test. If they are not normally distributed a Kruskal-Wallis test will be performed with the addition of separate Mann-Whitney U tests as post-hoc tests. The significance of these separate Mann-Whitney U tests will be corrected for multiple testing using the Bonferroni Holm method.

Using the means and standard deviations mentioned above, with an alpha of 0.025 (corrected for multiple testing using the Bonferroni Holm method) and a  $\beta$  of 0.20 this would require a total of 139 patients per group if the results are normally distributed and 146 patients per group if they aren't. A total of 156 patients per group will be included, to account for loss to follow-up, deaths etc. Which amounts to a total of 468 patients. Calculation was done by using the program G-power.

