## 1. Introduction

Community-acquired pneumonia (CAP) is a common and serious illness. In developed countries it is the most important cause of death due to an infectious disease and in the Netherlands it is the fourth leading cause of death overall.

In CAP caused by bacteria prompt initiation of antibiotic therapy is recommended, since a delay might be associated with increased mortality. The optimal duration of antibiotic therapy in bacterial CAP remains unknown. Most likely, it varies from patient to patient.

Current guidelines recommend treatment duration of 7-21 days, depending on illness severity and type of pathogen. However, adherence to guidelines is variable and physicians tend to treat longer, especially in patients with comorbidities and patients with severe CAP. Duration of treatment can be guided by clinical signs, but interpretation of the clinical response lacks standardization and is prone to interobserver variability.

A new approach to estimate the presence of an infection and response to treatment is the use of biomarkers. Circulating levels of calcitonin precursors, including procalcitonin are elevated in bacterial infections. Procalcitonin can follow either a classic hormonal expression pathway or in the presence of an infection, a cytokine-like expression pathway.

The release of procalcitonin during infection can be induced either directly by microbial toxins such as endotoxin and indirectly by humoral factors such as IL-1 $\beta$ , TNF- $\alpha$  and IL-6 or the cell-mediated host response.

Several studies have shown procalcitonin can be used as a marker for bacterial lower respiratory infections and CAP. Some studies demonstrate procalcitonin can be used effectively and safely as a marker to initiate or discontinue treatment with antibiotics. However only one of these trials focuses on patients with CAP admitted to hospital. One of our objectives is to validate the procalcitonin based treatment strategy mentioned by Christ Crain et al. and Long et al.

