## **6.4 Study procedures – detailed overview.**

### **6.4.1 Day 1 – hospital admission.**

At the baseline visit (hospital admission, day 1), subjects will be deemed eligible to take part in the study after the clinical diagnosis of Community Acquired Pneumonia has been made. The following procedures will be completed:

1. Verify inclusion/exclusion criteria
2. Obtain written informed consent
3. Record medical history
4. Collection of demographic information, concurrent disease, concomitant medication use and previous antibiotic therapy.

5. Physical examination (including but not limited to: mild/moderate/severe illness, sputum characteristics, cough, dyspnoea, pleuritic chest pain, chills or rigors and lung sounds) and vital signs (blood pressure, heart rate, temperature, respiration rate and oxygen saturation) will be recorded.
6. The CURB-65 score will be determined. (**C**onfusion, **U**rea > 7 mmol/l, **R**espiratory rate ≥30/min, diastolic **B**lood pressure ≤ 60 en age ≥ **65** years)
7. Blood and urine sample for routine laboratory testing and inflammation study will be obtained.
8. Chest X-rays will be made, if possible both PA and lateral views will be obtained. An AP chest X-ray will be considered acceptable if the patient is unable to stand.
9. Blood cultures will be obtained for all. All blood cultures will be assessed by the laboratory of medical microbiology. All isolates will be tested for susceptibility.
10. If possible an adequate sputum sample will be collected for conventional microbiologic assessment as well as PCR assays and delivered expeditiously to the laboratory to ensure a viable specimen. Freshly expectorated purulent sputum samples must be examined macroscopically for consistency and colour and microscopically to determine the suitability for culture. The presence of > 25 polymorphonuclear leucocytes and < 10 squamous epithelial cells per low power field of a Gram stained specimen is defined as "representative" sputum. Only "representative" sputum specimens as determined by Gram stain should be cultured. If medically indicated, the investigator may attempt to obtain other lower respiratory secretions such as bronchial washing and Broncho Alveolar Lavage (BAL) obtained by bronchoscopy. The specimens will be handled in the same way as sputum specimens.
11. Urine will be collected for detection of *S. pneumoniae* urinary antigen and for *Legionella pneumophila* (subtype 1) urinary antigen.

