## **8.2 Randomisation method**

Randomisation will be done by using block-randomisation with a block size of 30 patients, which amounts to a total of 15 blocks of 30 patients and 1 block of 18 patients. The allocation ratio in each block will be 1:1:1. So each block will contain 10 patients getting treated according to Common Clinical Practice, 10 patients getting treated according to the CRP guided strategy and 10 patients getting treated according to the PCT guided strategy. The last block will contain 6 patients in each treatment group.

Each centre will start with a single block, upon completion they will be assigned the next available block. For example if centre A starts with block 1 and centre B starts with block 2, the centre who includes the first 30 patients will be assigned block 3. The main-investigator will be responsible for maintaining this list and appointing blocks to each centre.

No stratification will be performed, since there are no known or expected variables to warrant stratification.

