## **8.4 Methods of analysis**

### **8.4.1 General statistical considerations**

All data will be collected and analysed using SPSS statistics 20.

Statistical analysis will be performed on an intent-to-treat basis by an independent statistician. All continuous variables will be tested for normal distribution with the Kolmogorov-Smirnov test for normal distribution. The Student-t test will be used for normally distributed variables, the Mann-Whitney U test for not normally distributed variables and the  $\chi^2$  test for dichotomous variables. The software package SPSS 20 for Windows (IBM-SPSS Inc., Chicago, Illinois, USA) is available for statistical analysis. A value of  $p < 0.05$  will be considered significant.

All data will be collected and analysed using SPSS statistics 20.

Clinical response will be analysed by using the Kruskal wallis test.

Duration of treatment and in-hospital stay will be expressed as means with a 95% confidence interval. Sub-group analyses will be performed on patients with severe CAP according to the CURB criteria and patients with non-severe CAP.

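### The primary tests of antibiotic duration use no baseline covariate, and any adjustment for severity is left open, although CURB-65 is scored on day 1: a cheap gain in precision, not an error of validity

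*Protocol*

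**What the plan says.** The primary analysis compares days of antibiotic treatment between each guided arm and common practice (Protocol 4.4 and 8.1). The tests are fixed in the protocol itself: "If they are normally distributed an ANOVA will be performed, with the addition of a Tukey-HSD test", and otherwise Kruskal-Wallis followed by Mann-Whitney tests with a Holm correction. Treatment arm is the only factor in both routes.

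Severity appears in several other places:
- Section 1 ties guideline duration to severity and pathogen, and adds that "physicians tend to treat longer, especially in patients with comorbidities and patients with severe CAP".
- Section 6.4.1: "The CURB-65 score will be determined". This is item 6 of the day-1 list; randomisation is item 15.
- Section 8.4.2 uses CURB-65 for the baseline comparison.
- Section 8.4.1: "Sub-group analyses will be performed on patients with severe CAP according to the CURB criteria and patients with non-severe CAP".
- Section 8.4.3 names antibiotic duration as the primary efficacy analysis. It then says that possible confounders will be looked at, giving co-morbidities and pathogen as examples, and corrected for if that seems appropriate.
- Sections 6.2 and 8.2: "No stratification will be performed, since there are no known or expected variables to warrant stratification".

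**The concern.** The protocol identifies severity as a driver of the quantity it will test and records it before allocation. It then uses severity neither in the allocation nor in the named primary tests. Variation in duration that day-1 severity could explain therefore stays in the error term, and a chance difference in severity between arms stays in the estimate.

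The clause in 8.4.3 does not settle this. It does not list severity, gives no model, and makes the correction depend on a judgement for which no rule is set. In an open-label trial (section 3), that lets adjustment of the primary outcome be decided after the data are seen. At stake are the width of the confidence intervals, some power (mainly for the PCT comparison, where the pooled SD is larger), and a primary result that does not depend on a later choice.

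**Working it through.** **Inputs from section 8.1.** Difference of 2 days. SDs 5.87499 (common practice), 4.80257 (PCT) and 3.61518 (CRP). Power 0.80. Type I error "with an alpha of 0.025 (corrected for multiple testing using the Bonferroni Holm method"). Planned enrolment is 156 per group; section 4.4 prints 148, but 468 / 3 = 156.

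**Step 1: reproduce the plan.** For a normal outcome the protocol states "of 0.20 this would require a total of 139 patients per group if the results are normally distributed". For the rank route its figure is 146 per group.
- Pooled SD, PCT and control: √[(4.80257² + 5.87499²)/2] = 5.366, so d = 2/5.366 = 0.373.
- Two-sample t-test (noncentral t), two-sided 0.025: 139 per group, power 80.3%. This matches.
- Rank test with relative efficiency 3/π = 0.955: 139/0.955 = 145.6, rounded up to 146. This matches. (Solving directly with that efficiency gives 145.)
- Other readings do not fit: one-sided 0.025 gives 114, the CRP pooled SD (4.878) gives 115, and the listed mean differences of 2.48 and 3.63 days give 91 and 36.

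The stated sample size is thus correct for an unadjusted comparison.

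**Step 2: unadjusted power at 156 per group.** The standard error for PCT versus control is 5.366 × √(2/156) = 0.608 days. Power is 85.0% for PCT and 91.4% for CRP (t-test). For the rank test, PCT power is 83.2%. These figures take all 156 as analysed, before any losses.

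**Step 3: effect of adjusting for CURB-65.** With correlation ρ between CURB-65 and duration within arms, residual SD = 5.366 × √(1 − ρ²). A chance imbalance in the covariate moves the unadjusted difference by up to 1.96 × ρ × 0.608 days at its 95% limit. The documents give no ρ, so the whole column is an assumption.

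| Assumed ρ | Variance explained | SE, PCT vs control (days) | t-test power, PCT, n = 156 | 95% limit of shift from chance imbalance (days) |
|---|---|---|---|---|
| 0 | 0% | 0.608 | 85.0% | 0 |
| 0.1 | 1% | 0.604 | 85.4% | 0.12 |
| 0.2 | 4% | 0.595 | 86.5% | 0.24 |
| 0.3 | 9% | 0.580 | 88.4% | 0.36 |
| 0.5 | 25% | 0.526 | 93.9% | 0.60 |

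The shift in the last column is already part of the unadjusted standard error. It is not an extra error on top of it.

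**Step 4: limits of the table.** It applies one ρ to both arms and uses the linear-model formula. It does not give the gain for a rank test stratified into two severity groups, which was not computed.

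**The case against.** The strongest reply is that nothing here is invalid. Under randomisation the unadjusted comparison is unbiased and keeps its type I error, the sample size reproduces, and power exceeds 80% for both comparisons. All of that stands. A reader might infer that the trial is biased or underpowered for want of adjustment; the figures above do not support that.

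Second, severity is not ignored. It is in the baseline table and the subgroups, and 8.4.3 permits a correction. A reader might infer that the plan overlooks severity altogether, and that would be wrong. It is also fair that the exact covariate list often belongs in an SAP. But this protocol itself fixes the primary tests without a covariate, and the clause it adds leaves the decision to the data.

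Third, the sentence in 6.2 and 8.2 concerns stratified randomisation only. It gives no reason for leaving covariates out of the analysis and should not be read as one. Its conflict with section 1 is real, but narrower.

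Fourth, the gain rests on an assumed correlation, and there are grounds to expect a low one. Section 1 describes physician-driven treatment of severe CAP, not the CURB-65 score. In two of three arms stopping follows PCT or CRP (5.3, 5.4). In the control arm 5.2 sets 7 days if no complications occur, with lengthening left to the physician. That severity acts directly through 5.2 is an inference the document does not state. At ρ = 0.1 the gain is 0.4 points. This limits the size of the benefit; it does not remove it.

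**Conclusion.** The point holds as a cheap improvement. The primary tests in 4.4 and 8.1 omit a baseline covariate that the protocol collects and has reason to think prognostic, and 8.4.3 leaves any correction undefined. The cost is some precision and no adjustment for chance severity imbalance.

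For PCT versus control at 156 per group, prespecified adjustment would add between 0.4 and 8.9 points of t-test power for ρ from 0.1 to 0.5 (1.5 points at 0.2, 3.4 at 0.3). The lower part of that range is as plausible as the upper on what the documents say. These are t-test figures and do not carry over to the rank route. That route may well be the one used, since control durations range from 0 to 42 days around a mean of 8.76.

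Two parts do not depend on ρ: the open clause in 8.4.3 should be closed for the primary outcome, and the stratification statement should agree with section 1.

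**What to change.** 1. In 4.4/8.1 and 8.4.3, estimate each guided-versus-control difference in mean antibiotic days from a linear model with arm and day-1 CURB-65 score. Use robust standard errors, since the planning SDs run from 3.6 to 5.9, and apply the Holm correction to the two comparisons.
2. If the rank route is kept, use a van Elteren test stratified by the severe/non-severe split already planned in 8.4.1.
3. Keep the unadjusted comparison as a sensitivity analysis.
4. For the primary outcome, replace the open correction clause in 8.4.3 with this named covariate.
5. Reword the stratification rationale in 6.2 and 8.2 so that it no longer conflicts with section 1. Randomisation need not change.

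The cost is wording only: no new data, visits or patients. The downside is one extra covariate (or two strata) in the primary analysis and a slightly less simple presentation.

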## **8.2 Randomisation method**

Randomisation will be done by using block-randomisation with a block size of 30 patients, which amounts to a total of 15 blocks of 30 patients and 1 block of 18 patients. The allocation ratio in each block will be 1:1:1. So each block will contain 10 patients getting treated according to Common Clinical Practice, 10 patients getting treated according to the CRP guided strategy and 10 patients getting treated according to the PCT guided strategy. The last block will contain 6 patients in each treatment group.

Each centre will start with a single block, upon completion they will be assigned the next available block. For example if centre A starts with block 1 and centre B starts with block 2, the centre who includes the first 30 patients will be assigned block 3. The main-investigator will be responsible for maintaining this list and appointing blocks to each centre.

No stratification will be performed, since there are no known or expected variables to warrant stratification.

## **8.3 Analysis populations**

### **8.3.1 Clinical Intent-To-Treat (ITT) group**

All treated patients with clinical and radiological findings consistent with CAP will be included in the final ITT-population.

### **8.3.2 Per protocol analysis**

All patients who were diagnosed with CAP and received treatment according to study protocol will be included in the per protocol analysis.

Patients will be considered as non-evaluable if they fulfil the following criteria:

1. Study medication discontinued earlier than planned or less than 80% of study drugs taken.
2. Received concomitant systemic antibiotics for intercurrent illnesses.
3. No visit at evaluation point, unless subject was previously deemed a treatment failure.
4. Patients admitted to ICU
5. Death within the first 3 days of treatment.

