### **8.4.4 Clinical response analysis**

Clinical response to therapy will be assessed by the investigator at day 30. Clinical response will be based on the global assessment of the clinical presentation of the subject made by the investigator at the evaluation time point compared to the baseline assessment. Clinical outcome by the end of treatment will be cure, improvement, or failure. A clinical outcome of "cure" or "improvement" is considered a success. At the visit on day 30, the clinical outcome will be defined as successful, failure or relapse according to criteria specified in Appendix B.

"Intent to treat" and "evaluable" clinical analyses will be performed comparing clinical outcomes as defined on day 30. Ninety-five percent (95%) confidence intervals on the difference between the treatment groups in the rates of clinical success will be computed.

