|--------------------------------------------------------------------|------------------------------------------------------------------------------------------------------------------------------------------|
| Kwetsbaarheid (ernstig zieken, kwetsbare ouderen, jonge kinderen): | Ernstig zieke patiënten die een ICU opname behoeven zijn uitgesloten van deelname.
Ouderen zullen wel deel mogen nemen aan de studie. |

| Maatschappelijke risico's                                                |                                                                                                                  |
|---------------------------------------------------------------------------------|------------------------------------------------------------------------------------------------------------------|
| Voor de proefpersoon (privacy, stigmatisering, uitsluiting van verzekering):    | Geen.                                                                                                            |
| Voor het onderzoek (maatschappelijk draagvlak, gevoeligheid van het onderzoek): | Mogelijk eerste stap in nieuwe behandelstrategie op populatieniveau. Geen controverse op maatschappelijk niveau. |

| Risico's samenhangend met onderzoeksopzet en –uitvoering (risico op protocol violations) |           |
|-------------------------------------------------------------------------------------------------|-----------|
| Complexiteit van het protocol:                                                                  | Eenduidig |
| Aantal te includeren proefpersonen:                                                             | 468       |

| Conclusie risico-classificatie                 |                                                                                                                                                                                                                                                                                                                                                                                                                                                           |

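### The evaluable set drops ICU admissions at any time and applies an 80% drug rule that is undefined for biomarker-guided stopping, and the ITT set is not all randomised patients

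*Protocol*

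**What the plan says.** Section 8.3.1 defines the intent-to-treat population: "All treated patients with clinical and radiological findings consistent with CAP will be included in the final ITT-population". Sections 4.4 and 8.1 make this the population for the primary analysis of antibiotic duration and add a per-protocol analysis.

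Section 8.3.2 opens with an inclusion rule: "All patients who were diagnosed with CAP and received treatment according to study protocol will be included in the per protocol analysis". It then lists what makes a patient non-evaluable. The relevant items are:
- criterion 1: "Study medication discontinued earlier than planned or less than 80% of study drugs taken"
- criterion 3: "No visit at evaluation point, unless subject was previously deemed a treatment failure"
- criterion 4: "Patients admitted to ICU"
- criterion 5: "Death within the first 3 days of treatment"

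Section 8.4.4 compares clinical outcome in both populations. It says that intent-to-treat and evaluable "clinical analyses will be performed comparing clinical outcomes as defined on day 30", with 95% confidence intervals for the difference in success rates.

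Appendix B has its own 80% rule: at test of cure, a patient who got under 80% of the study drug for a reason other than clinical failure is indeterminate. Appendix A states "Ernstig zieke patiënten die een ICU opname behoeven zijn uitgesloten van deelname", that is, severely ill patients who need ICU are excluded from taking part. The exclusion list in section 4.3 has no such criterion.

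**The concern.** The trial asks whether antibiotics can be stopped earlier without harm, and clinical response at day 30 is part of the evidence on harm. Three rules weaken that evidence.

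First, criterion 4 has no time limit. An ICU admission after the arms diverge is among the worst outcomes that stopping too early could produce, and removing it takes exactly those cases out of the evaluable comparison.

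Second, criterion 1 is worded for a fixed course of a study drug. Here no drug is under test, and stopping is the intervention. The plan does not say what counts as planned, or 80% of what, when CRP or PCT decides the duration.

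Third, the ITT set depends on a judgement about diagnosis and treatment that can be made once allocation is known. Section 3 says there is no blinding.

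**Working it through.** **1. The plan's own figure.** Section 8.1 gives 139 patients per group if durations are normal and 146 if not. Inputs: difference 2 days; SDs 4.80257 (PCT) and 5.87499 (common practice); alpha 0.025, taken as two-sided; power 0.80. The pooled SD is sqrt((4.80257² + 5.87499²)/2) = 5.366. The noncentral-t calculation gives 139, and 139 × π/3 = 145.6, so 146. Both reproduce. Nothing below changes them.

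**2. ICU exclusion.** Within section 8.3.2, criterion 3 keeps a patient already scored as a treatment failure who then misses the visit, while criterion 4 removes a patient who reached ICU. The documents give no ICU rates, so the size is an illustration. Assume a failure rate of 8% among non-ICU patients in every arm, every ICU patient scored as a failure, and ICU admission of 3% in control. Failure rate in ITT = ICU rate + (1 − ICU rate) × 0.08.

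| ICU rate, biomarker arm | ITT failure, biomarker arm | ITT failure, control | ITT difference | Evaluable difference |
|---|---|---|---|---|
| 3% | 10.8% | 10.8% | 0 | 0 |
| 5% | 12.6% | 10.8% | 1.8 points | 0 |
| 8% | 15.4% | 10.8% | 4.6 points | 0 |
| 10% | 17.2% | 10.8% | 6.4 points | 0 |

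The evaluable difference is 0 in every row because, once ICU patients are gone, both arms fail at the assumed 8%. The harm shows in ITT and is lost in the evaluable set.

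**3. The 80% rule, read two ways.**

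*Against a 7-day course* (the uncomplicated control course in section 5.2): 0.8 × 7 = 5.6 days. A stop on day 4 is 4/7 = 57% and on day 5 is 5/7 = 71%. The planning means in section 8.1 are 5.1327/7 = 73% for CRP and 6.2832/7 = 90% for PCT. The share with a course under 5.6 days, from the means and SDs in section 8.1, depends on the assumed shape:

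| Arm (mean, SD) | Normal | Gamma | Lognormal |
|---|---|---|---|
| CRP (5.1327, 3.61518) | 55% | 64% | 68% |
| PCT (6.2832, 4.80257) | 44% | 54% | 57% |

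Of 156 per arm (468/3), that leaves between 156 × (1 − 0.675) = 51 and 156 × (1 − 0.551) = 70 CRP patients, and between 156 × (1 − 0.567) = 67.5 and 156 × (1 − 0.443) = 87 PCT patients, before other exclusions. A control who completes 7 days stays in.

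*Against the duration that the allocated strategy sets:* a patient who stops at the threshold has taken the whole planned course. About 0% are dropped for following the strategy.

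**4. Reach into ITT.** A biomarker-arm patient who stops on day 4 at the threshold and recovers is a cure under the second reading and indeterminate under the first. The ITT comparison uses the same Appendix B categories, so running it alongside does not remove this ambiguity.

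**5. ITT definition.** In section 6.4.1 eligibility is verified at step 1, randomisation is step 15 and treatment step 16. A further condition of being treated and having findings consistent with CAP can therefore only remove patients after randomisation.

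**6. ICU at entry.** Appendix A says patients needing ICU do not take part; section 4.3 does not list this; section 8.3.2 removes ICU patients from the evaluable set. The three places do not agree on whether ICU is an entry criterion or a later exclusion.

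**The case against.** **The ITT comparison protects the conclusion.** Section 8.4.4 plans it, sections 8.4.1 and 8.5 put analysis on an intent-to-treat basis, and section 8.3.1 removes neither ICU patients nor deaths. This stands. A reader might infer that the clinical comparison as a whole loses its failures; the documents do not support that, since only the evaluable comparison loses the ICU cases.

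**Early deaths.** A reader might infer that criterion 5 also hides harm from early stopping. It does not. Antibiotics are given in all arms on days 1–3 (section 5.1), guided stopping starts on day 4 (sections 5.3 and 5.4), and criterion 5 leaves later deaths in.

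**The 7-day denominator.** No section sets 7 days as the planned course in the biomarker arms, and the opening sentence of section 8.3.2 favours keeping patients treated as the protocol directs. A reader might infer that the rule does remove adherent biomarker patients and keep controls; that is only one reading. What stands is that the text does not settle between two readings with very different results. The shares in step 3 also rest on theoretical, retrospective durations.

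**ICU timing.** Given Appendix A, criterion 4 may have been meant for patients needing ICU at entry. That is possible, but as written it covers every ICU admission.

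**ITT.** Symptoms and new consolidation are entry criteria and treatment starts on day 1, so few patients are likely to be removed. This also stands.

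**Conclusion.** The point holds in limited form and should be fixed. Criterion 4, as worded, biases the evaluable day-30 comparison towards no difference. In the illustration it hides an excess of 1.8 to 6.4 points, which rests on assumed ICU and failure rates and on ICU patients being scored as failures; ITT still shows it. Criterion 1 is undefined for guided stopping: it removes roughly half or more of the biomarker patients under one reading and almost nobody for adherence under the other. Through Appendix B the same ambiguity enters the ITT endpoint. The ITT definition allows removal after allocation is known in an open-label trial, probably of few patients, and no material bias in the primary analysis is shown. No bias is claimed for criterion 5.

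**What to change.** - Section 8.3.1: define ITT as all randomised patients, analysed as allocated.
- Section 8.3.2: replace criterion 1 with adherence to the allocated stopping strategy, meaning that antibiotics were stopped or continued as that strategy directs.
- Section 8.3.2: delete criterion 4, so that ICU admissions after randomisation stay in the evaluable set and are scored under Appendix B. Simply counting every ICU admission and death as failure would conflict with Appendix B, which does not list ICU admission as failure and classes unrelated death as indeterminate.
- Appendix B: bring the 80% indeterminate rule into line with the same adherence definition.
- Reconcile the Appendix A statement on patients needing ICU with sections 4.3 and 8.3.2.

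The cost is wording only; 139 and 146 per group are unchanged. The downside is that a few misdiagnosed patients stay in ITT and slightly dilute the effect.
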